**Trial sponsor {5b}: Central Council for Research in Siddha**

**Role of study sponsor and funders {5c}:**

The funds from the granting will be used in procuring the COVID-19 kits, CBA biomarker kits and laboratory consumables etc. Funders will have no role in study design; data collection, management, analysis, and interpretation of data and writing or dissemination of the final report.

**Trial Coordination Center {5d}: Siddha Central Research Institute, Chennai**

A prospective, single centre, randomized open labelled comparative clinical study to evaluate the effectiveness of Siddha medicine, *Kabasura kudineer* and vitamin c-zinc supplementation in the management of asymptomatic COVID 19 patients.

## Introduction: {6a}

Coronavirus disease 2019 (COVID-19) is a respiratory tract infection caused by a newly emergent coronavirus, SARS-CoV-2, that was first recognized in Wuhan, China, in December 2019. While most people with COVID-19 develop mild or uncomplicated illness, approximately 14% develop severe disease requiring hospitalization and oxygen support and 5% require admission to an intensive care unit.(1) In severe cases, COVID-19 can be complicated by acute respiratory disease syndrome (ARDS), sepsis and septic shock, multiorgan failure, including acute kidney injury and cardiac injury. The mortality rate of COVID-19 is still increasing in other countries than China now. At present, there is limited evidence from randomized clinical trials to support any vaccines or pharmacological treatments from conventional medicine for COVID-19.(2)

According to Siddha system of medicine, the symptoms and signs of COVID-19 are identified as the aggravation of Iyam and which later associated with other Uyir thathukkal Vali and Azhal and expressed as Thontham (Mukkutram) leads to sannu.(3) Siddha medicine has played a major role in controlling the mortality rate of chikungunya and dengue in Tamil Nadu by administration of Nilavembu Kudineer during 2015.(4) Siddha medicine has contributed in lowering health burden during public health emergency. Siddha Medicine has a good potential to combat COVID-19(5).

## Rationale: {6b}

In this context, one of the classical formulations from Siddha system of medicine is *Kabasura kudineer* (KSK) consists of 15 herbals ingredients which individually has anti-viral activity (6). Cucurbitacin B (-112.09), Cardiolipide (-111.5), Apigenin (-98.84) and Pyrethrin (-92.98) presented in the KSK were found to be effective in preventing novel corona virus binding and replication.(7) Determination of organoleptic characters, preliminary phytochemical analysis, physico- chemical analysis, TLC photo documentation and HPTLC fingerprint studies on KSK were analyzed.(8) Toxicological study on KSK showed that it is safe(9). KSK also possess anti pyretic, anti-inflammatory and anti-bacterial effect. Vitamin c and zinc supplementation(CZ) is being prescribed for the COVID19 positive asymptomatic patients admitted in isolation ward. The role of CZ in the management of COVID19 is still not clear. Therefore, we propose to compare the effect of KSK and CZ in terms of negative conversion of SARS CoV- 2 infection.

## Objectives

### Primary:{7a}

- To determine efficacy of KSK compared with CZ in reducing the onset of clinical symptoms in asymptomatic patients
- To determine effectiveness of KSK compared with CZ in terms of reduction of SARS-CoV-2 viral load from the baseline
- To examine the effect of KSK compared with CZ on immune system in terms of selected immunological markers

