### Secondary:{7b}

To document

- Reduction in the risk of disease progression
- Accelerated recovery
- Reduction in intensive supportive care and long-term hospitalization
- Clinical profile in terms of Siddha System of Medicine (SSM)
- Adverse events/effects if any

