### Interventions Arm -1{11a}

#### **Kabasura Kudineer (Siddha Polyherbal decoction)**

Table 1: Composition of KSK

| S. No | Botanical name                 | Family         | Part Used   | Parts  |
|-------|--------------------------------|----------------|-------------|--------|
| 1.    | Zingiber officinale     | Zingiberaceae  | Rhizome     | 1 part |
| 2.    | Piper longum            | Piperaceae     | Fruit       | 1 part |
| 3.    | Syzygium aromaticum     | Myrtaceae      | Flower bud  | 1 part |
| 4.    | Anacyclus pyrethrum     | Asteraceae     | Rhizome     | 1 part |
| 5.    | Tragia involucrata      | Euphorbiaceae  | Leaves      | 1 part |
| 6.    | Solanum anguivi         | Solanaceae     | Leaves      | 1 part |
| 7.    | Terminalia chebula      | Combretaceae   | Fruit rind  | 1 part |
| 8.    | Justicia adathoda       | Acanthaceae    | Leaves      | 1 part |
| 9.    | Anisochilus carnosus    | Lamiaceae      | Whole plant | 1 part |
| 10.   | Costus speciosus        | Costaceae      | Rhizome     | 1 part |
| 11.   | Tinospora cordifolia    | Menispermaceae | Whole plant | 1 part |
| 12.   | Clerodendrum serratum   | Verbanaceae    | Leaves      | 1 part |
| 13.   | Andrographis paniculata | Acanthaceae    | Whole plant | 1 part |
| 14.   | Cyperus rotundus        | Cyperaceae     | Rhizome     | 1 part |
| 15.   | Sida acuta              | Malvaceae      | Whole plant | 1 part |

**SOP for preparation:** To 5g of KSK coarse powder, add 240 ml of water and allowed to boil till, it reduces to one-fourth (60ml) and filter the decoction (KSK).

**Dose** : 30 – 60 ml twice daily.  
**Dosage form** : Kudineer (decoction).  
**Route of administration** : Oral.  
**Time of administration** : twice a day- Morning and Night before food  
**Duration of therapy** : 14 days  
**Follow up period** : 14 days after treatment

[illegible]

|                    |  |   |   |   |   |   |   |   |   |   |   |   |   |   |   |   |
|--------------------|--|---|---|---|---|---|---|---|---|---|---|---|---|---|---|---|
| SSM principles     |  | ✓ | ✓ | ✓ | ✓ | ✓ | ✓ | ✓ | ✓ | ✓ | ✓ | ✓ | ✓ | ✓ | ✓ | ✓ |
| Laboratory Markers |  | ✓ |   |   |   |   |   | ✓ |   |   |   |   |   |   |   | ✓ |

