### Specimen labelling and processing

Personal protective equipment (apron, hand gloves, face shield, N95 Masks etc.) will be used and all biosafety precautions will be followed so as to protect individuals and the environment. Proper labelling (name/age/gender/specimen ID) will be done on specimen container and other details of sender (name/address/phone number) on the outer container by mentioning “KSK\_COVID\_trial”

[figure not shown]

Figure 1: Lab Specimen collection

Laboratory sample collection Schedule: (i) Oropharyngeal swabs (0,7,14 days) - for SARS-CoV-2 RT-PCR (samples will be transported to Laboratory, as per the guidelines); (ii) Blood sample (0,7,14 days) (iii) ECG, Xray (Base line)

All samples would be stored for future-related tests.

Table 4: Schedule of investigations

| Parameter              | D0 | D7 | D14 |
|------------------------|----|----|-----|
| Haemogram\$            | ✓  | ✓  | ✓   |
| *LFT                   | ✓  |    | ✓   |
| #RFT                   | ✓  |    | ✓   |
| HbA1c, BS              | ✓  |    |     |
| qRT- PCR for SARS Cov2 | ✓  | ✓  | ✓   |
| Electrolytes           | ✓  | ✓  | ✓   |
| Chest X-ray            | ✓  |    |     |
| ECG                    | ✓  |    | ✓   |
| Immunoglobulins        | ✓  | ✓  | ✓   |

\$Hb%, total leucocyte count and differential WBC -neutrophils, lymphocytes, eosinophils, monocytes and basophils, RBC count, platelet count; #Renal function test -BUN, Creatinine; \*Liver function test -albumin, bilirubin, ALT, AST, alkaline phosphatase. AST, aspartate transaminase; ALT, alanine aminotransferase; RBC, red blood cell; WBC, white blood cell; BUN, blood urea nitrogen; ECG, electrocardiogram; SARS-CoV-2, severe acute respiratory syndrome coronavirus 2; qRT-PCR, real-time reverse transcription-polymerase chain reaction; HbA1c, haemoglobin A1c; Hb, haemoglobin

Frequency and duration of monitoring: (i) Patients will be monitored daily until discharge from the hospital and followed up till 14 days;

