### Outcome assessment

Clinical outcomes: (i) Assessment of clinical symptoms (ii) Clinical profile of SSM (iii) Time to test COVID-19 Negative

Safety Assessment: (i) Elevation of ALT to more than five-fold upper normal limit; (ii) Anaphylaxis; and (iii) Adverse events and serious adverse events.

Laboratory outcomes: (i) Viral RNA loads and cycle threshold values in serial samples of nasopharyngeal

and oropharyngeal swabs and blood, collected every week (to document anti-viral activity). (ii) Immunoglobulins values in serial samples of serum collected every week (to document immunomodulatory effect)

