### Data Analysis plan {20}

The analysis plan on the primary and secondary outcome is described in the below table

Table 5: Statistical analysis plan{20a}

| Outcome                                                              | Hypothesis                                 | Outcome measure                                        | Methods of analysis            |
|----------------------------------------------------------------------|--------------------------------------------|--------------------------------------------------------|--------------------------------|
| Primary                                                       |                                            |                                                        |                                |
| Viral load of SARS-CoV-2                                             | Reduction of Viral Load after intervention | Viral Load                                             | T test                         |
| Immunological markers                                                | Improvement                                | Th1, Th2 cells                                         | T test                         |
| Secondary                                                     |                                            |                                                        |                                |
| Reduction in the risk of disease progression                         | Reduction of complication                  | Incidence of complication                              | Kaplan Meier survival analysis |
| Reduction in intensive supportive care and long-term hospitalization | Reduction of complication                  | Incidence of complication                              | Kaplan Meier survival analysis |
| Clinical profile in terms of Siddha System of Medicine (SSM)         |                                            | Questionnaire                                          | Chi-square test                |
| Adverse events/effects                                               |                                            | Presence of drug related adverse event (time to event) | Kaplan Meier survival analysis |

**Data monitoring {21a}:** The data safety monitoring committee constituted by Ministry of AYUSH will be responsible for the monitoring the data

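### Symptom onset is the first of three primary objectives, but the analysis table has no row for it, so no planned analysis compares the arms on it

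*Protocol*

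**What the plan says.** Objectives, Primary {7a}, lists three primary objectives. The first is "To determine efficacy of KSK compared with CZ in reducing the onset of clinical symptoms in asymptomatic patients". The second concerns viral load and the third concerns selected immune markers.

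The Data Analysis plan {20} opens with "The analysis plan on the primary and secondary outcome is described in the below table". The table that follows is Table 5, headed as the statistical analysis plan. Its primary block has two rows: viral load, with the hypothesis "Reduction of Viral Load after intervention", and immunological markers, measured as Th1 and Th2 cells. Both are to be analysed by t test. The secondary block has four rows.

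Outcome assessment names "Assessment of clinical symptoms" as the first clinical outcome, with no event definition, time point or comparison attached. Data collection {19} provides for an examination and a question about complaints at every visit.

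Follow-up is described twice. Interventions Arm 1 {11a} gives 14 days of therapy and then a follow-up period of "14 days after treatment". Specimen labelling and processing says "Patients will be monitored daily until discharge from the hospital and followed up till 14 days".

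**The concern.** The objectives and the analysis table disagree about what the primary outcomes are. Everyone enters the trial without symptoms (Eligibility criteria {10}), so every participant is at risk of this event. It is also the only primary objective that a patient would notice, since the other two are laboratory measures.

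If the table is followed as written, two laboratory comparisons become the primary result and the question listed first has no prespecified estimate. Because there is no blinding {17a,b}, and symptoms depend on reporting and judgement, it matters that the event, the window and the comparison are fixed beforehand. If they are not, they can be chosen once the data by arm are visible.

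**Working it through.** The protocol gives no figure to reproduce on this point. The check matches each primary objective to the rows of Table 5.

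| Primary objective {7a} | Primary row in Table 5 | Method |
|---|---|---|
| 1. Symptom onset | none | none |
| 2. Viral load | viral load | t test |
| 3. Immune markers | Th1, Th2 cells | t test |

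Count: 3 primary objectives, 2 primary rows, 3 − 2 = 1 objective without a row.

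Next, could one of the four secondary rows serve in its place?

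- **Disease progression.** The measure is "Incidence of complication", by Kaplan-Meier. Secondary {7b} lists "Reduction in the risk of disease progression" as an objective in its own right, apart from symptom onset. A first symptom in someone who had none is not the same event as a complication.
- **Intensive care and long stay.** This row uses the same complication measure, so the same reasoning applies.
- **Siddha clinical profile.** This is a questionnaire analysed by chi-square. Outcome assessment lists it as an item separate from clinical symptoms.
- **Adverse events.** The row counts drug-related events, which is not symptom onset from the infection.

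Rows that cover symptom onset: 0 of 6.

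Finally, the window. Under Interventions, 14 days of therapy plus 14 days afterwards is 14 + 14 = 28 days from the start. The sentence under Specimen labelling and processing does not say what its 14 days are counted from. They could run from the start of treatment, from its end, or from discharge. The two statements may or may not agree, so neither can be used as the counting window until they are reconciled.

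**The case against.** Three arguments on the other side deserve weight.

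**The data will exist.** Symptoms are a named clinical outcome, patients are seen daily until discharge, and complaints are asked about at every visit. This stands. A reader might infer that the trial can never answer its first question, but the documents do not support that. What is missing is a planned comparison; the observations are provided for.

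**The definition may be elsewhere.** Part of the Interventions section is illegible, the item labels jump from {11a} to {14}, and Table 2 is not visible. An outcome definition or visit schedule may have stood there, and a separate analysis plan may exist. This stands as a limit: it cannot be said that the event is undefined in the full protocol. It does not remove the mismatch, because Table 5 reads as complete and says that it covers the primary outcome. A later plan that added symptom onset as primary would be departing from that table.

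**This is a 60-patient pilot.** That bears on how firm any conclusion could be. It does not explain why a declared primary objective has no analysis.

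**Conclusion.** The point holds as an inconsistency within the protocol: one of three primary objectives, the first listed and the only clinical one, has no row in the table that claims to set out its analysis. It needs correction, and the correction is small. The conclusion rests on reading Table 5 as complete and on the legible text alone.

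Three stronger inferences are not supported:

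- **The window differs by a factor of two, day 14 against day 28.** This depends on one reading of a phrase with no stated anchor. The wording is ambiguous; a contradiction has not been shown.
- **Observation ends at a time that depends on outcome.** Daily monitoring does stop at discharge, but no legible text gives a discharge criterion.
- **The trial is too small for this endpoint.** The protocol gives no expected symptom rate and states that no sample size assumptions could be made. Any power figure would rest on invented rates and would describe 30 patients per arm, not the missing row.

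**What to change.** Do one of two things.

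1. Add a primary row to Table 5 for symptom onset. For example: the proportion of all randomised patients with any new symptom within one fixed window, identical in both arms and unaffected by when a patient is discharged, reported as a risk difference with 95% CI. An estimate with its interval suits a 60-patient pilot.
2. If symptom onset is not meant to be primary, move it out of the primary objectives so that they match Table 5.

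Under the first option, reconcile the two follow-up statements (Interventions Arm 1, and Specimen labelling and processing) before the window is set, and say what each 14 days is counted from. Which length is right is for the investigators to decide.

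The cost is a wording change and a small amount of analysis. Under the first option, patients discharged before the window closes also need a status check. No new type of measurement is required.

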### Secondary:{7b}

To document

- Reduction in the risk of disease progression
- Accelerated recovery
- Reduction in intensive supportive care and long-term hospitalization
- Clinical profile in terms of Siddha System of Medicine (SSM)
- Adverse events/effects if any

## Proposed methods

### Study design {8}:

- Randomized, open-label, clinical trial

Study Setting {9}:

COVID Care Centre managed by Government Stanley Medical College, Chennai

### Eligibility criteria {10}

#### Study participants

##### **Inclusion**

1. Laboratory confirmed COVID-19 without symptoms
2. Aged 18-55 years
3. Consenting to participate in the study and sign the informed consent

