##### **Exclusion**

1. Patient with co morbid conditions like DM, HT, BA
2. Patients with severe primary respiratory disease or other pathogenic microbial pneumonia that needs to be identified with COVID-19
3. Pregnant and mothers, those who have a pregnancy plan.
4. Patients with other systemic malignant diseases such as malignant tumors, mental illnesses, etc., which the researchers consider unsuitable for participation in the study
5. People who have been allergic to Siddha medicine or intolerant to taking medicine
6. Patients participating in other COVID-19 clinical trials

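### Entry and analysis are not tied to a positive day-0 PCR, so patients with no viral load to lose could enter and dilute the viral-load comparison

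*Protocol*

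**What the plan says.** Inclusion 1 (Protocol, Eligibility criteria {10}) reads "Laboratory confirmed COVID-19 without symptoms". The other two inclusions are "Aged 18-55 years" and consent. The six exclusions cover comorbidity, other respiratory disease, pregnancy, malignancy or mental illness, allergy or intolerance, and "Patients participating in other COVID-19 clinical trials". None concerns stage of infection.

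Three primary objectives are listed under Primary {7a}. The first concerns "reducing the onset of clinical symptoms in asymptomatic patients". The second concerns effectiveness "in terms of reduction of SARS-CoV-2 viral load from the baseline". The third concerns immunological markers. Outcome assessment adds time to a negative COVID-19 test, and the Rationale {6b} gives negative conversion as the purpose of the comparison.

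The sampling schedule has "Oropharyngeal swabs (0,7,14 days) - for SARS-CoV-2 RT-PCR". Data collection {19} includes an illness history at recruitment. Both are recorded, but neither is a condition of entry. Table 5 assigns a t test to viral load and states no rule for a patient who is negative at day 0. The sample size is 60, 30 per arm, described as a pilot without a calculation.

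**The concern.** A reduction from baseline needs virus at baseline, and a time to negative needs a positive start. The entry rule secures neither. A confirming sample may precede day 0 by any interval, and infection clears without treatment, so someone who has already cleared the virus still meets the criterion as written.

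A patient negative at day 0 is at the floor of the viral-load scale, and that patient's time to a negative test is zero or undefined. If such patients stay in the t test, they contribute no treatment difference in either arm and pull the estimate towards zero. Patients who are late in the infection but still positive can show a fall, though they have less room for it. A pilot meant to supply the assumptions that its sample-size section lacks would then hand a diluted estimate to the next trial.

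**Working it through.** **The plan's own figure.** Two groups of 30 make 60, as stated. No alpha, power, effect size or SD is given, so the sample size cannot be reproduced. What follows illustrates the mechanism and does not check a stated figure.

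**Entry rule set against outcomes**

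| Outcome | What it needs at day 0 | Secured by the entry criteria? |
|---|---|---|
| Viral-load reduction from baseline (primary) | Detectable virus | No |
| Time to a negative test | A positive test | No |
| Symptom onset (primary) | No symptom so far | Probably intended, not defined |
| Immunological markers (primary) | Neither of these | Not affected by this point |

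**Inputs.** From the Protocol: n = 30 per arm, comparison by t test. Assumed: two-sided alpha 0.05; a share f in each arm with no possible response; SD unchanged by the mixture; normal approximation.

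**Step 1: effect with 80% power when f = 0.**
d = (1.960 + 0.842) × √(2/30) = 2.802 × 0.2582 = 0.72 SD.

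**Step 2: dilution.** With a share f contributing zero difference, the observable difference is (1 − f)d, and power = Φ(2.802(1 − f) − 1.960). The n per arm that restores 80% power is about 30/(1 − f)².

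| f (assumed) | Diluted effect (SD) | Argument of Φ | Power | n per arm for 80% |
|---|---|---|---|---|
| 0 | 0.72 | 0.842 | 80% | 30 |
| 10% | 0.65 | 0.561 | 71% | 38 |
| 20% | 0.58 | 0.281 | 61% | 47 |

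**Step 3: what restriction recovers.** If day-0-negative patients are left out, the full effect is estimated on 30(1 − f) per arm, and power = Φ(2.802√(1 − f) − 1.960).
- f = 10%: 27 per arm, Φ(0.698) = 76%.
- f = 20%: 24 per arm, Φ(0.546) = 71%.

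Restriction therefore recovers part of the loss. It does not return to 80%, because the excluded patients are not replaced.

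**Step 4: chance imbalance.** Assume 12 of 60 patients (20%) are non-informative and the arms are 30/30. The hypergeometric probability that the arms differ by four or more such patients is 33%. This is chance, not bias, but an unadjusted comparison leaves it in the result.

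**The case against.** **The setting points to recent diagnosis.** Patients come from a COVID Care Centre, and the Rationale speaks of patients admitted to isolation. This makes long intervals less likely, but it sets no limit. The text shows that day-0-negative patients could enter, not that they will be common.

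**Recovered patients.** A reader might infer that someone whose symptoms have just resolved is eligible. The documents do not support that firmly. The title, Rationale and first primary objective all speak of asymptomatic patients, so the natural reading of inclusion 1 is asymptomatic infection, and the illness history would reveal earlier symptoms. What remains is a missing definition.

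**Late patients.** A reader might also infer that anyone late in the infection cannot respond. That is strictly true for viral load only when the day-0 swab is negative.

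**Symptom onset.** It is tempting to apply the (1 − f)² loss here too. For a proportion, the variance falls as the rates are diluted. With assumed onset rates of 40% and 10%, f = 20% gives 32% and 8%. The relative information is (0.24²/0.2912)/(0.30²/0.33) = 0.73, an effective n of about 44 out of 60, where 0.8² would give 38. The power figures above apply to viral load only.

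**Pilot status and an unseen SAP.** No stated power is lost, because none is stated. A SAP might already restrict the analysis set or adjust for baseline, but it cannot change who is enrolled, and the Protocol's own Table 5 names a plain t test. The scheduled day-0 PCR would at least make an imbalance visible.

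**Conclusion.** The point holds as a gap between who may enter and what the virological outcomes require. Patients who are PCR-negative at day 0 are admissible, cannot contribute to viral-load reduction or negative conversion, and are not set aside in the analysis as described. The viral-load difference shrinks to (1 − f) of its size. Under the stated assumptions, 80% power becomes about 71% at f = 10% and 61% at f = 20%.

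The value of f, the unchanged SD and the alpha level are assumptions; the documents give none of them. Randomization spreads these patients over both arms on average, so the cost is precision, with some exposure to chance imbalance in a trial of 60. A reader might infer systematic bias in favour of one arm, or that all primary objectives are compromised. Neither follows: allocation is random, and the immunological objective depends on neither a positive swab nor remaining symptom risk.

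**What to change.** 1. State that the day-0 swab is taken before the first dose.
2. Restrict the viral-load and time-to-negative comparisons to patients whose day-0 swab is positive. Because the swab precedes treatment, this does not break the randomized comparison.
3. In Table 5, replace the plain t test on viral load with a between-arm comparison adjusted for day-0 viral load or cycle threshold, such as analysis of covariance.
4. Record the number of days from the first positive sample to randomization.
5. State in inclusion 1 that the absence of symptoms means no COVID-19 symptom so far in this infection.

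The investigators may also set a maximum interval from the positive sample, but no particular number of days follows from the documents.

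The cost is a few lines of text and one case report form field. The day-0 PCR and illness history are already collected, so no test is added. The downside is that day-0-negative patients leave the virological analysis, so its n falls somewhat below 30 per arm (27 at an assumed 10%, 24 at 20%). They remain in the trial for the other outcomes.
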